## Abstract

**Background:**

Affecting adolescent and young adults, anorexia nervosa (AN) has the highest death rate of all mental disorders. Effective treatment options are lacking and a significant proportion of patients develop severe and chronic forms of the disease with long-lasting functional impairment. Neurobiology of AN implicates the nucleus accumbens as a core structure of the ventral striatum highly connected to the prefrontal cortex, the insula and the limbic system. Several studies reported promising results of deep brain stimulation for treatment-resistant AN. The aim of this study was to investigate the safety and efficacy of bilateral nucleus accumbens deep brain stimulation in severe and enduring AN.

**Methods and analysis:**

This is a prospective, multicentre, single-arm, open-label, non-randomized pilot trial of bilateral nucleus accumbens deep brain stimulation for severe and enduring AN. Patients will be followed up for 24 months after deep brain stimulation. The main objective of this study is to measure the safety and feasibility of nucleus accumbens deep brain stimulation in this population. The recruitment rate will be collected prospectively. Potential deep brain stimulation efficacy will be monitored by changes in: 1) health-related quality of life; 2) weight; 3) eating disorder symptomatology; 4) neuropsychological changes of cognitive flexibility, habits formation, emotional processing and central coherence; 5) psychiatric comorbidities (anxiety, depression, obsession). Local field potential recordings during an exposure task will be proposed to the patients. Additionally, caregiver quality of life will be assessed.

**Discussion:**

We present the design and rationale for a pilot study investigating the safety of nucleus accumbens deep brain stimulation for treatment resistant anorexia nervosa. This trial will provide an estimated effect size of nucleus accumbens deep brain stimulation for treatment-resistant anorexia nervosa to support future larger-scale clinical trials.

## Introduction

1

### Background and rationale

1.1

Anorexia nervosa (AN) is the psychiatric disorder with the highest mortality rate – the standardized mortality rate is higher than four – due to somatic complications and suicide (1–3). The median age at onset of AN is 15.5 years old (4). Despite the lack of longitudinal data and significant heterogeneity of care pathways, approximately 20% of patients develop a long-lasting disorder (5). In a staging approach, this subgroup of patients is considered to suffer from “severe and enduring AN” (SE-AN). Patients with SE-AN may benefit from specific treatments focusing on improving their social functioning and quality of life (6). At present, treatments for SE-AN are largely lacking (7).

The core position of the nucleus accumbens (NAc) is now well described in AN (8). NAc is involved in top-down control in decision-making through a fronto-accumbal hyperconnectivity (9), in food choice (10), and in body image disturbance through its connectivity with the insula (11). Numerous studies identified the mesocortico-limbic dopaminergic system in controlling eating behavior and body weight (12–15). Projections from the ventral tegmental area to the NAc are largely involved in the motivational aspect of food intake (16). Functional neuroimaging studies performed on acute and weight-recovered patients show that the NAc is a key structure associated with remission after refeeding (9, 17). The specific faculty to delay reward, as measured by the delay discounting task, involves the NAc (17). Preclinical studies identified an imbalance between ventral (NAc) and dorsal (caudate/putamen) striatum for the transition from reward-guided and goal-directed behaviors to automatic habitual behavior (18). These compulsive behaviors are common to both AN and obsessive-compulsive disorder (19).

Deep brain stimulation (DBS) of the NAc in mouse models of AN shows increase of food intake (20, 21) while, in a domestic pig model, DBS of the NAc shows modulation of the activity of the reward circuit structures (22). Recent series have reported promising results with NAc deep brain stimulation in patients suffering from severe and enduring AN (23–25).

Several promising reports concerning DBS in patients suffering from SE-AN have been published (23–31). In particular, the seminal studies by the group of Toronto showed that surgery and DBS are well tolerated in this population (28, 29). Nevertheless, these previous studies present some limitations. First, the DBS target was not systematically designed for AN. Second, included patients had frequently a very low body mass index (BMI). The BMI increase should not be the only studied endpoint since medical treatment alone cand lead to an acceptable BMI in AN (32–35). BMI is influenced by many variables other than pathophysiological improvement in the subpopulation of patients with SE-AN. Repetitive inpatient treatment can temporarily increase or stabilize BMI without quality of life improvement. While BMI at discharge remains a well-characterized prognostic factor (36, 37), recent studies have highlighted the need for a harm reduction-based treatment (38). Pilot studies assessing treatment acceptability and tolerability are necessary to explore the possibility of a subsequent larger, randomized, trial (39, 40).

### Objectives

1.2

The main objective of the present study is to assess the feasibility and the safety of NAc DBS – during a single-stage surgery or two-staged surgery - in patients with SE-AN. Serious adverse events following DBS surgery will be monitored. The secondary objective is to measure the efficacy of NAc DBS. Clinical variables concerning recruitment rate, changes in BMI, changes in neurocognitive impairment, and changes in quality of life for the patient and their caregiver, will be prospectively collected. Local Field Potential (LFP) while performing provocation task will be recorded during two-staged surgery. This prospective pilot trial will help to build a larger randomized trial.

### Trial design

1.3

We present the protocol for a multicentre, prospective, open-label, uncontrolled interventional trial, of bilateral NAc-DBS for SE-AN. The trial is currently open for recruitment at the GHU Paris Psychiatrie et Neurosciences Sainte Anne Hospital (Paris, France) and at the Clinique Villa Montsouris (Paris, France). These centers are specialized for the management of patients suffering from eating disorders abiding to the criteria of the French Federation Anorexia Bulimia and the General Directorate of Healthcare [Direction Général de l’Offre de Soins]: the teams from GHU Paris Psychiatrie et Neurosciences Sainte Anne Hospital and Clinique Villa Montsouris are working together (even before this trial) in the Ile-de-France TCA network (Réseau TCA Francilien; https://www.reseautca-idf.org/) and participate to the monthly multidisciplinary meeting attended by psychiatrists, psychologists, neurologists, neuroradiologists and neurosurgeons (https://www.ghu-paris.fr/fr/rcp-neuromodulation). In this way, prior to applying for grant funding, all referring physicians have given their consent to participate. They have received specific training by psychiatric and neurological teams of the GHU Paris Psychiatrie et Neurosciences already trained in deep brain stimulation programming.

## Methods

2

### Study setting

2.1

This is a multicentre, prospective, uncontrolled interventional trial with repeated pre- and per-stimulation measurements. The population of interest is patients suffering from SE-AN. After enrolment, patients will perform a complete preoperative workup, including metabolic assessment, neurocognitive evaluation, including emotional processing to specific AN stimulus, brain MRI. A DBS system will be implanted during surgery under general anesthesia. A 24-month follow-up will allow to observe and manage, if necessary, possible DBS-related complications and to perform two postoperative workups. DBS parameters will be optimized during this 24-month follow-up.

The sponsor of this study is the GHU Paris Psychiatry and Neurosciences, an academic hospital located in the fourteenth district of Paris (France). It is responsible for monitoring the study. It received a grant from the French Ministry of Health via the Programme Hospitalier de Recherche Clinique Interrégional 2019 (AOR19101-[name]). No company is involved in funding this study.

### Participants

2.2

The three different inclusion centers are all located in the Ile de France (Paris area) region. Two of them are university hospitals: 1) GHU Paris Psychiatry and Neuroscience Sainte Anne (Paris, France), 2) Paul Brousse Hospital (Public Assistance - Paris Hospitals, Paris, France), while the other one is a private clinic: 3) Clinique Villa Montsouris (CLINEA, Paris, France). They have a dedicated unit for eating disorders and are recognized as nationwide expert centers according to the French Federation Anorexia Bulimia (https://www.ffab.fr/).

Potential participants are reviewed by the investigators concerning inclusion and exclusion criteria (**Table 1**). The most important criterion is the definition of chronic and treatment-resistant anorexia nervosa (41, 42). This criterion is a composite criterion: 1) minimum duration of the anorexia nervosa of 7 years; 2) failure of at least two hospitalizations in a specialized center during the history of the disease, more precisely inability to maintain a BMI ≥ 17kg/m² for 2 months following hospitalization in a specialized center for the management of patients suffering from eating disorders (abiding to the criteria of the French Federation Anorexia Bulimia and the General Directorate of Healthcare [Direction Général de l’Offre de Soins]); 3) failure of at least two outpatient treatments conducted by a specialized team during the history of the disease (including at least one during the year preceding inclusion), in detail inability to maintain a BMI ≥ 17kg/m² for more than three consecutive months while following an outpatient treatment conducted by a specialized center for the management of patients suffering from eating disorders (abiding to the criteria of the French Federation Anorexia Bulimia and the General Directorate of Healthcare [Direction Général de l’Offre de Soins]). Eligible patients are discussed in a multidisciplinary meeting of the psychiatric, neurological, neuroradiological, and neurosurgical teams. Patients presenting both anorexia nervosa and bulimia nervosa are not excluded. There are no changes to the participants’ medical or psychotherapeutic/behavioral treatment(s) after enrolment before surgery. Any changes to treatments following surgery are documented, including dosages and indications for change.

**Table 1 T1:** Study inclusion and exclusion criteria.

Inclusion Criteria
1. Presence of Anorexia nervosa according to DSM V criteria. 2. Age 18 to 65 years. 3. Chronic, treatment-resistant anorexia nervosa, defined as:
- Anorexia nervosa evolving for at least 7 years - Inability to maintain a BMI ≥ 17kg/m² for 2 months following hospitalization in a specialized center for the management of patients suffering from eating disorders (abiding to the criteria of the French Federation Anorexia Bulimia and the General Directorate of Healthcare [Direction Général de l’Offre de Soins]). Failure of at least 2 hospitalizations in a specialized center during the history of the disease. - Inability to maintain a BMI ≥ 17kg/m² for more than 3 consecutive months during the year preceding the inclusion, while following an outpatient treatment conducted by a specialized center for the management of patients suffering from eating disorders (abiding to the criteria of the French Federation Anorexia Bulimia and the General Directorate of Healthcare [Direction Général de l’Offre de Soins]). Failure of at least 2 outpatient treatments conducted by a specialized team during the history of the disease
4. Impaired psychological, social, and occupational functioning defined by a score ≤ 45 on the Global Assessment of Functioning Scale. 5. Anorexia nervosa is judged to be the primary disorder if there are psychiatric comorbidities such as depression, anxiety disorder, obsessive-compulsive disorder, or personality disorder, by at least two independent experts. 6. The patient is able to comply with the operational and administrative requirements of the study and is able to complete the protocol questionnaires. 7. Patient provides written informed consent. 8. Patient is drug-free or on a medication that has been stable for at least 6 weeks at the time of the study entry. 9. If female subject and of childbearing age: use of an effective method of contraception. 10. Patient has health insurance.
Exclusion Criteria
1. Presence of a concurrent major clinical disorder (Axis I disorder) that is primary toanorexia nervosa confirmed by both a clinical interview and a structured interview. 2. Presence of a personality disorder assessed by structured interview that could compromise compliance with post-surgical follow-up according to 2 independent psychiatrists 3. Presence of severe neurological pathology or significant MRI abnormalities (excluding anorexia-related atrophy). 4. Cognitive and intellectual capacity to understand the risks and constraints of the technique or to give informed consent. 5. Albumin levels <30g/L. 6. Presence of medical contraindications to undergo implantation of a deep brain stimulation system or to receive an MRI (non-MRI compatible pacemaker for instance). 7. Pregnant or breastfeeding woman. 8. History of deep brain stimulation for anorexia nervosa or other pathology. 9. Contraindication to general anesthesia. 10. Presence of multiple comorbidites or active generalized infections. 11. Patient deprived of liberty by judicial or administrative decision. 12. Patient under forced psychiatric care. 13. Patient admitted to a health or social institution for purposes other than research. 14. Minor patient (under 18 years of age). 15. Patient under legal protection (guardianship, curatorship). 16. Patient unable to give consent.

### Intervention: DBS surgery

2.3

The experimental medical device is a DBS device: Infinity™ system. It is composed of two DBS directional electrodes (6172), extensions (60 cm if possible to ensure the MRI compatibility, or 90 cm if not possible), and the non-rechargeable implantable neurostimulator. The manufacturer is the ABBOTT Laboratories (Abbott Park, IL, USA). The treatment, i.e. high-frequency electrical stimulation, is then delivered continuously and over the long term. The hospitalization in neurosurgery lasts seven days.

The different stages of the DBS surgical procedure at GHU Paris Psychiatrie et Neurosciences Sainte Anne are:

The patients undergo a preoperative MRI scan. This MRI is performed on a 3-T Vantage Galan ZGO scanner (Canon Medical Systems Corporation, Otawara, Japan). The sequences are the following: 1/three-dimensional (3D) T1-weighted fast spoiled gradient-recalled acquisition; 2/two-dimensional (2D) coronal accelerated fast spin echo scan T2-weighted focused on nucleus accumbens; 3/Spin Echo DTI 50 directions; 4/3D Susceptibility-weighted angiography sequence; 5/3D CUBE Fluid attenuated Inversion recovery; 6/3D CUBE T2-weighted; 7/contrast material–enhanced three-dimensional (3D) T1-weighted fast spoiled gradient-recalled acquisition (gadoterate meglumine [Dotarem; Guerbet, Aulnay-sous-Bois, France], 0.1 mmol/kg).Surgery consists of fitting two DBS electrodes, the extensions (cables linking the electrodes to the neurostimulator) and the neurostimulator. The surgery (in one stage or in two stages) takes place under general anesthesia. It is performed with a robotic arm (Neuromate, Renishaw) and an intraoperative 3D imaging device (O-Arm 2.0, Medtronic). Depending on patient agreement, this surgery may be carried out in one stage or in two stages.

The one-stage surgery consists of a unique procedure during which the electrodes are implanted and connected to the extensions, which in turn are connected to the neurostimulator.

During the two-stage surgery, the leads are connected to externalized temporary extensions first. The patient is then discharged from the operating theatre and LFP are recorded (see below). After 4 days, the patient returns to the operating room, the temporary extensions are removed and the electrodes are connected to the permanent extensions, which in turn are connected to the neurostimulator.

C. Post-operative monitoring systematically involves post-operative imaging and biological sampling in addition to the clinical checks (healing follow-up, neurological examination, evolution of the symptoms of the SE-AN). On day 1 after the lead implantation, a postoperative biological sampling and a CT scan (LightSpeed; GE Healthcare, Milwaukee, Wisconsin, USA) without contrast enhancement are performed to check the correct positioning of the electrodes and the absence of postoperative biological and radiological complications. A second follow-up CT scan may be discussed, given the possible movement of the directional stimulation electrodes at a distance from the surgery. This second CT head scan may therefore be carried out three months after the electrodes have been implanted, to ensure that the positioning of the directional contacts has not changed.

During the first postoperative week, neurostimulation is started on the following parameters: 2 mA – 90µseconds – 130 Hertz using the adapted tool (Physician programming system, Apple™ Ipad Mini, ABBOTT). At day 7, i.e. at the theoretical discharge of the patient, the patient’s notebook and patient card are handed over, and the following neurostimulation parameters (4 mA – 90 µseconds – 130 Hertz using the adapted tool) are set.

The eventual subsequent changes in the stimulation parameters are left to the discretion of the research team and are validated during a multidisciplinary meeting. In this way, programming the DBS system is performed by a member of the research team during a visit in addition to the usual check-ups (see below). The medical treatment can be changed during the stimulation period: all modification is recorded into a dedicated eCRF (see below).

### Outcomes

2.4

#### Primary endpoint

2.4.1

The primary endpoint is the proportion of serious adverse reactions (SAR) occurring in the patients included in the study. For continuous safety monitoring, we adopt a binomial sequential test, re-evaluated with each new patient, with the following parameters: maximum proportion of patients with SAR 15%, bilateral alpha 15%, beta 20%. The maximum and minimum tolerance limits for SAR were determined using the toxbdry function of the clinfun package version 1.0.15 of R. Taking the lower limit as a precaution, **Table 2** summarizes the maximum number of patients with a tolerable SAR to respect a threshold below 15%. This study design is justified because complications directly related to surgery typically appear within the first month (43). There are long-term complications of DBS which are taken into account in the protocol as the patients are followed up (44). These long-term complications must be put into perspective with the risk of death associated with SE-AN (2). The first three patients will be included sequentially with an interval of at least one month to ensure that there are no systematic adverse effects. If the 15% threshold of SAR in the study population is exceeded, as assessed in a sequential procedure, the study will be stopped.

**Table 2 T2:** Maximum number of patients with a serious adverse event to respect a threshold below 15%.

Number of included patients	Maximum limit of the interval
3	1
4	1
5	1
6	1
7	1
8	2
9	2
10	2
11	2
12	3

Highlighted numbers correspond to the maximum tolerated threshold of patient(s) presenting a serious adverse reaction related to the surgery (rounded down).

Serious adverse events are defined by the French National Agency for the Safety of Medicines and Health Products (ANSM) based on the French Public Health Code: “A serious adverse event is an adverse event that is lethal, or likely to be life-threatening, or leading to significant or lasting disability or incapacity, or causing or prolonging hospitalization, or manifesting itself as a congenital anomaly or malformation.”

SAR are serious adverse events directly caused by the intervention. In particular, we look for:

Intracerebral hematoma directly related to surgery resulting in permanent neurological deficit,Cerebromeningeal infection directly related to surgery resulting in a life-threatening condition during treatment,Development of drug-resistant epilepsy directly related to the surgery and affecting the patient’s quality of life,Permanent neurological deficit(s) induced by the activation of the brain stimulation,Major psychiatric impairment directly related to the surgery and endangering the patient’s vital prognosis.

Four different levels of causality are used: 1) Not related; 2) Possible; 3) Probable; and 4) Causal relationship. The intensity of the adverse events is assessed using the Common Terminology Criteria for Adverse Events (Version 5.0, Published: November 27, 2017).

Concerning any eventual SAR, the causality will be discussed during a meeting with the Independent Monitoring Committee. For instance, suicide or suicide attempts could be or not be directly related to the surgery (45). Indeed, Parkinson’s disease patients operated with deep brain stimulation demonstrated a lower risk of suicide relative to Parkinson’s disease patients without deep brain stimulation (46). At first, any serious adverse event (such as a suicide) will result in the protocol being stopped until the cause of this possible SAR is characterized.

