### Participant timeline

2.5

A detailed schedule for trial participants is presented in **Table 4**.

**Table 4 T4:** Detailed schedule for trial participants.

Assessment	*Visit(s) with the referring physician* (prior to the trial)	Eligibility Visit 1 -4 weeks	Enrollment Visit 2 Week 0	Preoperative Visit 3 weeks after Visit 2	Surgery 4 weeks after Visit 3	Postoperative Visits 5-29					End of trial Visit 30 24 months after surgery (+/- 1 week)	*Post-trial* At least every 3 months
						Every month (+/- 1 week)	Every 2 months (+/- 1 week)	3 months after surgery (+/- 1 week)	12 months after surgery (+/- 1 week)	23 months after surgery (+/- 1 week)		
Eligibility screen	**X**	**X**										
Informed consent for trial			**X**									
Care-taker informed consent for trial			**X**									
Informed surgical consent				**X**								
Neurosurgical examination			**X**	**X**	**X**		**X**					**X**
Psychiatric examination		**X**	**X**		**X**	**X**						**X**
Body Mass Index measurement		**X**	**X**	**X**	**X**	**X**	**X**	**X**	**X**	**X**	**X**	**X**
Serious Adverse Events monitoring				**X**	**X**	**X**	**X**	**X**	**X**	**X**	**X**	**X**
Anesthetic evaluation				**X**								
Biological tests				**X**	**X**							
MRI				**X**								
Deep brain stimulation surgery					**X**							
Postoperative CT					**X**							
The Eating Disorder Inventory 2				**X**				**X**	**X**	**X**		
Psychiatric Scales												
1. Hospital Anxiety and Depression Scale 2. Yale Brown Obsessive-Compulsive Scale 3. Scale for Suicide Ideation				**X**				**X**	**X**	**X**		
Neurocognitive Scales												
1. Montreal Cognitive Assessment 2. Delay Discounting Task 3. Wisconsin Card Ranking Test 4. Brixton Test 5. Trail Making Test A and B 6. Slip-of-action test 7. Habits vs Goal Directed Behavior test 8. Dubois Five Word Test 9. Rey/Taylor Figure				**X**				**X**	**X**	**X**		
Quality of life Scales												
1. SF-36 Quality of Life Questionnaire 2. Global Assessment of Functioning Scale				**X**				**X**	**X**	**X**		
Care-taker Scale												
1. Zarit Burden Inventory (to be completed by the care-taker)				**X**				**X**	**X**	**X**		
Pupillometry				**X**				**X**	**X**	**X**		

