Patients are informed by their referring practitioner of the existence of the protocol and the surgical possibilities before the selection visit (so outside the trial itself). Patients eligible for inclusion are discussed at a multidisciplinary meeting attended by psychiatrists, psychologists, neurologists, neuroradiologists, and neurosurgeons. Referring practitioners work in reference centers for the management of anorexia nervosa: patients deemed clinically or psychologically unstable are not presented at the multidisciplinary consultation meeting. Only after a positive collegial opinion has been obtained from the multidisciplinary consultation meeting can patients undergo the inclusion visit.

Patients who meet the inclusion criteria and do not have exclusion criteria are informed about the protocol during the selection visit. The inclusion visit takes place at least 2 weeks after the protocol description: this is a mixed consultation necessarily associating a psychiatrist specialized in the management of eating disorders and a neurosurgeon specialized in DBS. The patient’s trusted person and/or his relatives is present during this consultation. During the inclusion visit, the patient is asked to give or not his consent to participate in the study. The necessary steps before a DBS surgery (anesthesia assessment, MRI, blood tests) and the first neurocognitive assessment are performed during the preoperative visit. The patient has at least three visits and 8 weeks between the selection visit and the surgery.

The duration of follow-up after patient inclusion is 24 months. The patient is followed up at least monthly by the referring physician. These visits are part of the patient’s routine care: their frequency can therefore be modulated according to the care required but can never be less than monthly. The minimal investigations conducted during these consultations are as follows: 1) structured psychiatric interview; 2) measurement of BMI; 3) collection of SAR; 4) verification of the functioning (impedance measurement in particular) of the neurostimulation using the appropriate equipment (Physician programming system, Apple™ Ipad Mini, ABBOTT).

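### The primary SAR proportion and Table 2 count consented rather than operated patients, which dilutes the rate and can loosen the stopping limit

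*Protocol article*

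**What the plan says.** All references are to the protocol article.

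- **Denominator (2.4.1).** "The primary endpoint is the proportion of serious adverse reactions (SAR) occurring in the patients included in the study".
- **Stopping table (Table 2).** The row index is headed "Number of included patients". The tolerated number of patients with a SAR is 1 for rows 3 to 7, 2 for rows 8 to 11, and 3 for row 12.
- **Action (2.4.1).** "If the 15% threshold of SAR in the study population is exceeded, as assessed in a sequential procedure, the study will be stopped".
- **Numerator (2.4.1).** "SAR are serious adverse events directly caused by the intervention".
- **Moment of inclusion (2.5).** "During the inclusion visit, the patient is asked to give or not his consent to participate in the study". Table 4 dates this visit as week 0.
- **Moment of surgery (Table 4).** The preoperative visit follows enrolment by 3 weeks, and then comes "Surgery 4 weeks after Visit 3". MRI, blood tests, anesthetic evaluation and surgical consent all belong to the preoperative visit.
- **Spacing (2.4.1).** The first three inclusions are at least one month apart, in order to rule out systematic adverse effects. The design is justified by surgical complications usually showing within a month.

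**The concern.** Numerator and denominator refer to different populations. Only an operated patient can have a SAR, but every consented patient counts from week 0. This has two consequences.

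1. A patient who is included and never operated stays in the primary denominator as a patient without an event, so the reported proportion is too low.
2. A patient who is included and still waiting for surgery moves the reading of Table 2 to a higher row without adding any exposure. Where that row carries a larger limit, an excess of SAR is tolerated for longer.

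Both errors favour continuing, in a 12-patient surgical trial whose primary endpoint is safety.

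**Working it through.** **Table 2 as printed.** The article says: "The maximum and minimum tolerance limits for SAR were determined using the toxbdry function of the clinfun package version 1.0.15 of R". That function needs an unacceptable rate, which the article does not give, and the table could not be reproduced from the stated 15% threshold, 15% alpha and 20% beta. This is a separate matter. The limits are taken as printed below.

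**Schedule.** Inclusion to surgery is 3 + 4 = 7 weeks, or 49 days. The eligibility visit is 4 weeks before inclusion, so selection to surgery is 4 + 3 + 4 = 11 weeks, consistent with the minimum of 8 weeks in 2.5. At that minimum the lag from inclusion to surgery would be 8 − 4 = 4 weeks.

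**Step 1: final proportion.** If k of 12 included patients are not operated, the reported value is x/12 and the risk among those exposed is x/(12 − k). The relative understatement is k/12. The article gives no k, so a range is shown for x = 3:

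| k | reported | among operated |
|---|---|---|
| 0 | 3/12 = 25% | 3/12 = 25% |
| 1 | 3/12 = 25% | 3/11 = 27.3% |
| 2 | 3/12 = 25% | 3/10 = 30% |
| 3 | 3/12 = 25% | 3/9 = 33.3% |

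Accrual plays no part in this step.

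**Step 2: where the limit moves.** The limit rises only at rows 8 and 12. With 2 patients waiting, 8 included means 6 operated, so 2 SAR are tolerated where the row for 6 allows 1. Likewise 12 included means 10 operated, so 3 are tolerated where the row for 10 allows 2. Between those steps the index makes no difference.

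**Step 3: exact stopping probability at a true risk p = 0.30.** Let X_m be the number of patients with a SAR among the first m operated. The trial continues to the end only if the count stays within the limit at the last row of each flat stretch.

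- *Indexed by operated patients:* continue if X_7 ≤ 1 and X_11 ≤ 2 (X_12 ≤ 3 then holds). P(X_7 = 0) = 0.7^7 = 0.0824 and P(X_7 = 1) = 7 × 0.3 × 0.7^6 = 0.2471. For the next four patients, P(≤ 2) = 0.9163 and P(≤ 1) = 0.6517. P(continue) = 0.0824 × 0.9163 + 0.2471 × 0.6517 = 0.2365. P(stop) = **0.764**.
- *One patient waiting:* continue if X_6 ≤ 1, X_10 ≤ 2 and X_12 ≤ 3. P(X_6 = 0) = 0.1176 and P(X_6 = 1) = 0.3025. P(continue) = 0.1176 × 0.8925 + 0.3025 × 0.6147 = 0.2910. P(stop) = **0.709**.
- *Two patients waiting:* continue if X_5 ≤ 1, X_9 ≤ 2 and X_12 ≤ 3. P(X_5 = 0) = 0.1681 and P(X_5 = 1) = 0.3602. P(continue) = 0.1681 × 0.8480 + 0.3602 × 0.5563 = 0.3429. P(stop) = **0.657**.

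At a true risk of 7/16 = 43.75%, the proportion cited in 2.8.1, the same three readings give 94.6%, 92.6% and 90.6%.

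**Step 4: dependence on accrual.** A simulation checked the limit whenever a SAR occurs. It assumed p = 0.30, onset uniform over the first postoperative month, and equally spaced inclusions.

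| Inclusion interval (assumed) | P(stop), included | P(stop), operated |
|---|---|---|
| 1 month | 0.68 | 0.76 |
| 2 months | 0.73 | 0.76 |
| 3 months | 0.76 | 0.76 |

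At monthly inclusion the mean number operated is 7.3 against 6.8. Under these assumptions the effect is gone once the interval exceeds about 49 + 30 = 79 days, because the next patient is then not yet included when the SAR appears.

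**Step 5: the first row.** At the minimum spacing, patient 3 is included at about day 61, patient 1 was operated on day 49, and patient 2 is due at about day 30 + 49 = 79. One operated patient cannot exceed a limit of 1, so row 3 cannot trigger at that moment.

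**The case against.** The strongest reply is that included is loose wording for operated. Section 2.4.2.1 times the neuropsychological assessments from inclusion, while Table 4 and the rest of 2.5 time them from surgery. The footnote of Table 2 speaks of reactions tied to the surgery, and the first-month rationale makes sense only from surgery. This probably describes the intent. It does not rescue the text: inclusion is a defined, dated visit, and a stopping rule must have one reading.

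A second reply is that analysis sets and patients who are not implanted are usually left to the full protocol or analysis plan. That would answer a missing definition. Here the article itself states the denominator and the table index.

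A third reply is that 2.4.1 halts the protocol after any serious adverse event until its cause is characterised, with the Independent Monitoring Committee discussing causality. This is a real safeguard and softens the practical effect. It leaves the denominator and the later reading of Table 2 unchanged.

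Three stronger readings should be resisted. A reader might infer that Table 2 is always read two or three rows too high. The article gives no accrual rate, the lag is 1 or 2 patients at inclusion intervals of one to two months, and the limit changes only at 8 and 12. A reader might infer that clearly more patients will be operated. At monthly inclusion the difference is about half a patient (7.3 against 6.8), and it vanishes with slow inclusion. A reader might assume that 10% or 20% of included patients are never operated. The documents support no such rate: a favourable multidisciplinary opinion precedes inclusion, and only the possibility of dropping out before surgery follows from the schedule.

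**Conclusion.** The point holds on the wording. The primary proportion and Table 2 count patients who cannot yet, or will never, have the event.

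- **Primary proportion.** It is understated by k/12 in relative terms if k of 12 are not operated. This holds at any accrual rate; the value of k is unknown.
- **Stopping limit.** At a true risk of 30%, the stopping probability falls from 76% to 71% with one patient waiting and to 66% with two. This rests on an assumed lag and shrinks to nothing with slow inclusion.
- **First row.** At the minimum spacing, it cannot trigger when the third patient is included.

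Operated patients were probably intended, so the remedy is a correction of wording and not a redesign.

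**What to change.** 1. In 2.4.1 and the Table 2 heading, replace included by operated, defined as lead implantation performed.
2. Report the primary proportion over operated patients, and give the number included but not operated beside it.
3. Read Table 2 at the number of operated patients. State what postoperative observation makes a patient without an event count, in line with the article's own first-month rationale; a patient with a SAR counts at once. Say how the rule is read with fewer than three operated patients, since the table has no row below 3.
4. Reconcile the spacing of the first three patients, now stated from inclusion, with its stated purpose of detecting adverse effects.

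The cost is small: no new data and no new patients. The denominator may fall below 12, and the reported proportion may be slightly less favourable. A required observation period would also make each reading of the table somewhat later.
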